## 6.1 Population

All patients scheduled for a carpal tunnel release in the jessa hospital are eligible to partipate.

## 6.2 Inclusion criteria:

- - Males and females ≥ 18 years of age
  - American Society of Anesthesiology (ASA) physical status classification: 1-3
  - Patients planned to undergo carpal tunnel release via regional anesthesia (intravenous regional anesthesia or ultra-sound guided peripheral nerve block)

## 6.3 Exclusie criteria:

- - Bilateral surgery
  - BMI ≥ 40 kg/m2
  - Infection in the area of the peripheral nerve block injection site
  - History of neurological conditions
  - Chronic pain symptoms
  - Concomitant use of Opioids in the last 3 months
  - Diabetes mellitus type-1 (insulin dependent diabetes mellitus)
  - Diabetes mellitus with organ damage
  - Oversensitivity to local anesthesia
  - Blood clotting disorder
  - History of any surgical procedure in the arm that needs to be operated
  - Inability to understand and adhere to the study design

## 6.4 Sample Size Calculation

Sample size was determined for the primary study outcome with the aim to reject the superiority of the distal peripheral nerve block compared to forearm intravenous regional anesthesia. Based on a retrospective analysis of unpublished data from our hospital, we assume that 75% of patients will have a complete block (grade 1 or2) after a forearm IVRA. Based on a previous study, we assume that 95% of patients will have a complete block (grade 1 or2) after a distal peripheral nerve block (4). By using a binary outcome, we determined the sample size for each group to be 47 (α=0.05, power=0.80). To account for a possible 6% drop-out rate, the sample size was increased to 50 patients per group.

1. **Study procedures**

**Pre-operatieve fase**

The patient will first receive information about this study during the consultation with the surgeon. After having ample amount of time to consider participation and before the start of the study, written informed consent will be obtained. Afterwards, the patient will be randomized to one of the 2 study groups.

Demographical data such as age, weight and lengthe together with preoperative NRS score will be assessed.

All anesthesia techniques will be performed by 4 anaesthesiologists, to reduce the inter-individual difference in anaesthesia. All patients will receive an intravenous catheter, supplementary oxygen and standard monitoring (non-invasive blood pressure, electrocardiogram and saturation measurements). General sedation is preoperative and perioperative not applied during day surgery.

The surgeon and the researcher will be blinded for the used type of anaesthesia. To reduce a possible deblinding, all patients receive a catheter in the dorsal vein of the hand that will undergo surgery and all patients will receive disinfection on the specific locations on the arm where the ultrasound-guided peripheral nerve block would be performed. In that way, both surgeon and researcher are blinded.

1. ***Distal peripheral nerveblock***

The distal peripheral nerve block will be performed in the local prick area 30 minutes before the surgery. A General Electric LOGIQe device and a 12 MHz lineair echotransducer with a foot of 4 cm will be used to locate the nervus medianus and the nervus ulnaris. In total, 10ml linisol 2% will be used to affect the nerves (3ml linisol 2% around the nervus medianus, 3ml linisol 2% around the nervus ulnaris and 4ml linisol 2% around the peripheral distal nerves).

The echoprobe is treated with sterile Tegaderm® foil and sterile echogel is used.

1. ***Mini-Bier block***

The Mini-Bier block will be performed in the opeation theathre, 5 min prior to the start of the surgery. An intravenous catheter will be placed in the dorsal vein of the hand that will undergo surgery. Also, a tourniquet will be placed on the forearm, after which the anesthetic can be administered via the dorsal vein catether (25ml linisol 0.5%).

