Secondary study outcomes are patient’s pre-, intra-, and post-operative pain scores at several time points, measured via an 11-point Numeric Rating Scale (NRS) in which number 0 means “no pain at all”, number 5 means “moderate pain” and number 10 means “worst possible pain”.

General patient satisfaction as well as satisfaction of the surgeon regarding the used technique will be measured via a 7-point Likert Scale, in which number 1 means “extremely dissatisfied” and number 7 means “extremely satisfied”.

Furthermore, the time spend in the operating room, the time of surgical procedure and the use of post-operative medication use will be recorded as well.

1. **Researchers**

[name], [name], [name]. [name]

Anesthesiology, Jessa hospital, Hasselt, België

[name]

Orthopedic Surgery, Jessa ziekenhuis, Hasselt, Belgium

1. **Funding**

This study received no funding.

1. **Outcome measures**

Results will be evaluated on day 0 during admission to hospital and on day 1 with a telephone call.

Primary outcome:

The primary outcome of this study is to compare the analgesic effectivity of the forearm intravenous regional anesthesia versus the ultrasound-guided distal peripheral nerve block. A blinded surgeon will determine the analgesic effectivity of these techniques after the patient is fully ready and surgically covered as this is an observed blinded study. The surgeon will grade the anaesthesia as “complete” or “incomplete” and divide the effectivity in 4 grades. Grade 1 and grade 2 are considered “complete” blockade, while grade 3 and grade 4 are considered “incomplete” blockade. Grade 1: complete motor and sensory blockade with a pincet in the medianus and ulnaris area, grade 2: partial motor blockade but no pain or deep pressure sensitivity, grade 3: partial motor blockade with mild pain requiring rescue local or opioid analgesia, grade 4: incomplete motor- and sensory blockade requiring sedation/conversion to general anesthesia).

Secondary outcomes:

- Pre-operative: pain score at start of anesthesia technique (measured via an 11-point Numeric Rating Scale)
- Pre-operative: pain score at surgical incision (start of surgical procedure) (11-point Numeric Rating Scale)
- Intraoperative: pain score (11-point Numeric Rating Scale) at every 10 min during the surgical procedure (both surgical pain and tourniquet pain)
- Time the patient is in operating room (start by entering the operating room until leaving the operating room)

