- Time of surgical procedure (start at surgical incision until closing of the surgical wound)
- Post-operative: average pain score at hospital discharge and at day 1 after surgery
- Post-operative: use of pain medication (paracetamol and/or ibuprofen) after surgery and at day 1 after surgery
- General satisfaction of the patient with the anesthesia technique (measured via a 7-point Likert scale with 1 absolutely not satisfied, 4 neutral and 7 extremely satisfied)
- Satisfaction of the surgeon with the surgical conditions (7-point Likert scale)

1. **Study design**

In this monocentric, investigator-initiated, observer-blinded, prospective, randomized controlled trial, 2 groups of patients that will undergo carpal tunnel release surgery will be compared.

Group 1: mini-Biers Block (standard of care in JESSA hospital)

Group 2: distal peripheral ultrasound-guided nerve block

This study will be performed according to the Declaration of Helsinki and will be approved by the Ethical Committee of the Jessa Hospital before the start of the study. A written informed consent will be obtained before participation in the study.

Randomization will be performed using a computer-generated random allocation sequence, created by the study statistician. Allocation numbers will be sealed in opaque envelopes, which will be opened in sequence by an independent anaesthesiologist who is not involved in the assessment of outcomes.

1. **Study population**

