**Safety**

All possible complications were explained to the participant preoperatieve. Both interventions, the distal peripheral nerve block and the mini biers block are standard techniques used in the Jessa hospital.

1. **Statistical analysis**

Sample size was determined for the primary study outcome with the aim to reject the superiority of the distal peripheral nerve block compared to forearm intravenous regional anesthesia. Based on a retrospective analysis of unpublished data from our hospital, we assume that 75% of patients will have a complete block (grade 1 or2) after a forearm IVRA. Based on a previous study, we assume that 95% of patients will have a complete block (grade 1 or2) after a distal peripheral nerve block (2). By using a binary outcome, we determined the sample size for each group to be 47 (α=0.05, power=0.80). To account for a possible 6% drop-out rate, the sample size was increased to 50 patients per group.

Descriptive statistics will be presented as frequencies and percentages of the total amount of patients for categorical variables, while numerical variables will be presented as mean ± SD. Group comparison will be performed using Chi-square test (or a Fisher’s Exact test when necessary) for frequencies. Depending on normality, a Mann-Witney U test or a Student’s t-test will be used and a Mixed-model analysis will be used to correct for the multiple measurements of the Numerical Rating Scale (NRS) for pain scores. An average difference of 1.3 points or more on the NRS pain score is considered clinical relevant. A p-value <0.05 is considered statistical significant, while p<0.10 is considered a tendency.

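### A preoperative NRS is collected from every patient but has no stated role in the NRS analysis, so precision on the secondary pain outcomes may be lost

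*Protocol*

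**What the plan says.** Under Study procedures, Pre-operatieve fase, the protocol lists age, weight and height, "together with preoperative NRS score will be assessed". This comes after the sentence on allocation: "Afterwards, the patient will be randomized to one of the 2 study groups". The exact order of the two steps is not fixed.

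The secondary outcomes under Outcome measures include these NRS scores:

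- "Pre-operative: pain score at start of anesthesia technique";
- a score at incision;
- "pain score (11-point Numeric Rating Scale) at every 10 min during the surgical procedure";
- "Post-operative: average pain score at hospital discharge and at day 1 after surgery".

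The Statistical analysis section provides for numerical data as follows: "Depending on normality, a Mann-Witney U test" or a t-test, and "a Mixed-model analysis will be used to correct for the multiple measurements of the Numerical Rating Scale (NRS) for pain scores". It names no covariate. It does not say which scores are responses, or whether a group main effect or a group-by-time effect is tested. It sets 1.3 NRS points as the clinically relevant difference.

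**The concern.** A score taken before treatment on the same scale as the outcome is often the most useful covariate a trial has. Here it is collected from everyone and then not mentioned again. If it stays unused, confidence intervals for the pain differences are wider than they need to be. Differences would then be harder to place above or below 1.3 points.

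A second pre-surgical score, at the start of the anaesthetic technique, is listed as an outcome beside the scores taken once the block should be working. The protocol does not say whether this is a baseline value or a record of pain caused by performing the technique, nor how it enters the repeated-measures model. What is at stake is efficiency and clarity on secondary outcomes.

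**Working it through.** **The plan's own figure.** The only sample size in the protocol is for the binary primary outcome. With complete-block rates of 75% and 95%, two-sided alpha 0.05 (sidedness is not stated) and power 0.80, the unpooled formula gives

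n = (1.960 + 0.842)² × (0.75×0.25 + 0.95×0.05) / 0.20² = 7.849 × 0.235 / 0.04 = 46.1, so 47 per group.

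Allowing for 6% drop-out, 47 / 0.94 = 50. The stated 47 and 50 reproduce, and nothing below changes them. The protocol gives no power calculation for NRS.

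**Inputs for NRS.** From the protocol: 50 per group and a relevant difference of 1.3 points. Assumed, because the protocol gives neither: the NRS standard deviation (2.0 to 3.0) and the correlation r between the preoperative score and a later score (0.1 to 0.5).

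**Precision gain from adjustment.** Adjustment multiplies the residual variance by 1 − r². The equivalent number of unadjusted patients per group is 50 / (1 − r²).

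| r | 1 − r² | variance reduction | equivalent n per group |
|---|---|---|---|
| 0.1 | 0.99 | 1% | 50.5 |
| 0.3 | 0.91 | 9% | 54.9 |
| 0.5 | 0.75 | 25% | 66.7 |

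**Power for 1.3 points at one time point.** The standard error is SD × √(1 − r²) × √(2/50), and power is Φ(1.3/SE − 1.96).

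Example with SD 2.5:
- Unadjusted: SE = 2.5 × 0.2 = 0.50, 1.3/0.50 = 2.60, power Φ(0.64) = 73.9%.
- With r = 0.5: SE = 0.50 × √0.75 = 0.433, 1.3/0.433 = 3.00, power Φ(1.04) = 85.1%.

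| SD | unadjusted | r = 0.1 | r = 0.3 | r = 0.5 |
|---|---|---|---|---|
| 2.0 | 90.1% | 90.4% | 92.6% | 96.3% |
| 2.5 | 73.9% | 74.3% | 77.8% | 85.1% |
| 3.0 | 58.2% | 58.6% | 62.2% | 70.6% |

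These are normal approximations. Scores under a working block may pile up near zero, so the figures are illustrative.

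**The start-of-technique score.** Under Study procedures, the nerve block is placed 30 minutes before surgery in the block area, and the mini-Bier block 5 minutes before surgery in theatre. The start of the technique is therefore a different moment and setting in each group. Whether the score records baseline pain or procedural pain, it does not measure analgesia from an established block.

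Suppose it carried no group effect, were one of K equally weighted responses, and the time-averaged group effect were tested. A true difference of 1.3 would then become 1.3 × (K − 1)/K: 0.87 for K = 3, 0.98 for K = 4, 1.04 for K = 5 and 1.08 for K = 6. With K = 4, SD 2.0 and within-patient correlation 0.5 (both assumed), power would be:

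- 86.9% with the early score as a response;
- 97.8% with the later scores only;
- 99.9% with the later scores adjusted for the early one.

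A test at each time point would show no such dilution.

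**The case against.** The strongest reply is that the protocol is silent, and silence is not a decision. Covariates and contrasts of a mixed model are commonly left to a statistical analysis plan, and that plan is not shown. This stands. A reader might infer that the trial has ruled out baseline adjustment, but the text neither includes it nor excludes it. What remains is that the stated method gives a collected baseline no role and that a better method is available from the same data.

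Four other inferences go further than the document:

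- **That the group effect is diluted.** This needs the start-of-technique score to be free of any group effect, to be a response in the model, and to be averaged into a single group effect. None of the three is stated.
- **That listing this score as an outcome is a mistake.** It may record pain from needle, tourniquet or injection, which is a legitimate comparison. The preoperative score may be a separate measurement.
- **That a normality check decides the NRS test.** The clause on the t-test and Mann-Whitney test may apply to other numerical variables, such as theatre time, with the mixed model reserved for NRS.
- **That the unadjusted comparison is biased by chance imbalance.** Randomisation makes it valid, and its standard error already reflects such imbalance.

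The gain could also be small. Most patients are expected to have a complete block (75% and 95%), and chronic pain and recent opioid use are exclusions. Both may weaken the link between preoperative and later scores.

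Finally, the preoperative score is described after randomisation, and only the observers are said to be blinded. Its standing as a clean baseline needs confirmation.

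**Conclusion.** The point holds as an inexpensive improvement to the secondary pain analyses. The preoperative NRS is collected, no analytic role is stated for it, and using it would cost nothing in data. Over the assumed range of r from 0.1 to 0.5, residual variance falls by 1% to 25%. At an assumed SD of 2.5, power for 1.3 points at a single time point would rise from 73.9% to between 74.3% and 85.1%. Both the correlation and the SD are assumptions. Validity of the randomised comparison, the primary outcome and the sample size are not in question. Dilution by the start-of-technique score is only a possibility that the present wording leaves open.

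**What to change.** In the Statistical analysis section, specify one mixed model for NRS:

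- **Responses:** the scores at incision, during surgery, at discharge and on day 1.
- **Terms:** group, time, group-by-time, and the preoperative NRS as covariate.
- **Report:** the adjusted mean difference with its 95% confidence interval at each time point, read against 1.3 points.

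Analyse pain at the start of the technique separately, and say whether it is meant as baseline or procedural pain and whether it is distinct from the preoperative score.

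In the Pre-operatieve fase text, confirm that the preoperative NRS is taken before the patient knows the allocation or is treated. If that cannot be confirmed, the score should not be used as a covariate without further justification.

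The cost is two or three sentences and a check on the timing of one measurement. No new data are needed and the sample size does not change.

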**Peri-operative phase:**

Before the start of the surgery, the surgeon will assess the quality of the block (primary outcome) in the nervus ulnaris and nervus medianus, using a forceps. The quality of the block will be graded “complete” (grade 1 and grade 2) or “incomplete” (grade 3 or grade 4). In case of grade 1 or grade 2, the surgical procedure can start. In case of grade 3, the blockade will be enhanced (local anesthetic for peripheral nerve block or intravenous opioid administration (alfentanil or sufentanil) for IVRA). In case of grade 4, sedation/conversion to general anesthesia will be performed.

Per-operative paracetamol administration 15mg/kg (max 1gram) and taradyl 0.5mg/kg (max 30mg) will be supplied (except when there are contraindications). All patients (both distal peripheral nerve block and IVRA) will receive dexamethasone 0.1mg/kg (max 5mg) (except when there are contraindications) due to the positive effect of dexamethasone on the extension of the locoregional anesthesia and the prevention of post-operative nausea and vomiting.

All secondary outcome measures will be investigated by the blinded researcher via questioning the patient’s pain scores (measured via an Numeric Rating Scale) at several time points before, during and after surgery, and the satisfaction of both patient and surgeon (measured via a 7-point Likert Scale).

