**Postoperative phase:**

Post-operative pain medication in the hospital includes paracetamol 15mg/kg (max 1gr) 1x/6h and taradyl 0.5mg/kg (max 30mg) 1x/8h, while contramal serves as rescue medication.

Post-operative pain medication at home includes paracetamol 15mg/kg (max 1gr) 1x/6h or ibuprofen 600mg 1x/8h whenever necessary.

On day 1 after surgery, the patient will be contacted via telephone by the researcher who will question the use of post-operative pain medication, as well as NRS pain scores and patient satisfaction.

1. **Randomisatie en blindering**

Participants will be randomly assigned to 1 of 2 study groups of 50 subjects each: ultrasound-guided peripheral nerve block group or forearm IVRA group. Randomization will be performed using a computer-generated random allocation sequence, created by the study statistician. Allocation numbers will be sealed in opaque envelopes, which will be opened in sequence by an independent anaesthesiologist who is not involved in the assessment of outcomes. Outcome-assessors (surgeon and study assistant) will be blinded to treatment allocation (observer-blinded study).

The surgeon and the researcher will be blinded for the used type of anaesthesia. To reduce a possible deblinding, all patients receive a catheter in the dorsal vein of the hand that will undergo surgery and all patients will receive disinfection on the specific locations on the arm where the ultrasound-guided peripheral nerve block would be performed. In that way, both surgeon and researcher are blinded.

Also, the surgeon and the assessor are asked to leave to operation room and only to enter after the patient is fully installed, desinfected and covered.

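### For secondary outcomes, the planned procedures do not secure the researcher's blinding: one score is due at the start of a technique whose place and time differ by arm, and grade 3 rescue is arm-specific and unmasked

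*Protocol*

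**What the plan says.** Under Outcome measures, the first secondary outcome is "Pre-operative: pain score at start of anesthesia technique (measured via an 11-point Numeric Rating Scale". The Peri-operative phase section states "All secondary outcome measures will be investigated by the blinded researcher via questioning the patient’s pain scores", at several times before, during and after surgery. The Postoperative phase section has the researcher make the day-1 call.

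The Pre-operatieve fase section places the two techniques differently. For one arm: "The distal peripheral nerve block will be performed in the local prick area 30 minutes before the surgery". For the other: "The Mini-Bier block will be performed in the opeation theathre, 5 min prior to the start of the surgery".

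The section Randomisatie en blindering states that surgeon and researcher are blinded. It relies on a hand-vein catheter and disinfection of the block sites in every patient, and adds that "the surgeon and the assessor are asked to leave to operation room and only to enter after the patient is fully installed, desinfected and covered".

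For a grade 3 block, the Peri-operative phase section says that "the blockade will be enhanced (local anesthetic for peripheral nerve block or intravenous opioid administration (alfentanil or sufentanil) for IVRA"). It describes no masking of this step.

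**The concern.** Two procedures can tell a blinded person which arm the patient is in.

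The first is the start-of-technique score. Someone present when the technique starts sees the room and how long before surgery it is, and both differ by arm. The catheter and the disinfection hide traces on the arm afterwards; they do nothing for an observer who was there at the start.

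The second is grade 3 rescue. It follows the surgeon's grading, when surgeon and researcher are already back in the room, and its form depends on the arm.

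At stake are the secondary outcomes collected afterwards: pain at incision, during surgery, at discharge and on day 1, patient satisfaction, and surgeon satisfaction. The trial would report them as observer-blinded although its own procedures do not secure this.

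**Working it through.** **Inputs.** Complete-block rates of 75% (IVRA) and 95% (nerve block), α = 0.05, power 0.80, 47 per group, 6% dropout and 50 per group all come from section 6.4, Sample Size Calculation. Place and time of each technique come from the Pre-operatieve fase section.

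**Step 1: reproduce the plan's figure.** With the two-sided unpooled normal approximation,

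n = (z₀.₉₇₅ + z₀.₈₀)² × [0.75 × 0.25 + 0.95 × 0.05] / (0.95 − 0.75)² = 46.1, rounded up to 47.

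Dropout: 47 / (1 − 0.06) = 50. The stated size reproduces, so its rates can be used below.

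**Step 2: the start-of-technique score.** The relevant statements, side by side:

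- The score is defined at the start of the technique (Outcome measures).
- All secondary outcomes go to the blinded researcher (Peri-operative phase). No section gives this score to anyone else.
- The technique starts in the prick area at −30 minutes in one arm and in theatre at −5 minutes in the other (Pre-operatieve fase).
- The assessor stays out of the operating room until the patient is covered (Randomisatie en blindering).

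If the researcher asks at the defined moment, place and time identify the arm in both groups: 50 + 50 = 100 patients. In the IVRA arm the researcher must also be in theatre when the rule says to be outside it. In the nerve-block arm the rule is not broken, because the prick area is not the operating room; there the arm is only inferred.

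If the researcher asks once the patient is covered, blinding is kept, but the score is no longer taken when it is defined. The recall interval then differs between arms by about 30 − 5 = 25 minutes. Neither reading satisfies all four statements.

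**Step 3: grade 3 rescue.** Expected incomplete blocks (grade 3 or 4):

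- IVRA: 50 × (1 − 0.75) = 12.5
- Nerve block: 50 × (1 − 0.95) = 2.5
- Total: 15 of 100

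With 47 per group the counts are 11.75 and 2.35. The protocol does not split grade 3 from grade 4, so the expected number receiving arm-specific grade 3 rescue lies between 0 and about 15.

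**Step 4: order of events for the primary outcome.** The surgeon enters after the patient is covered and grades the block; rescue follows from that grade. The surgeon does not collect the start-of-technique score. Neither route therefore reaches the primary outcome.

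**The case against.** The strongest reply is that the text does not put the researcher beside the patient when the technique starts. It speaks of questioning patients, which could be done later. The reference to all secondary outcomes is also loose, since operating-room time and surgical time are not obtained by questioning, and the Pre-operatieve fase section mentions a preoperative pain score without saying who takes it. This stands in part: exposure in all 100 patients is conditional on the researcher collecting the score in real time. It does not remove the inconsistency, because asking later changes what is measured, and the protocol neither says this nor names another person.

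A second reply is that pain scores and patient satisfaction are reported by patients, who are not stated to be blinded, so these outcomes are already open on one side. That is correct. It limits the added risk to interviewer bias, against which a blinded interviewer is the remaining protection. Surgeon satisfaction is different: it is the surgeon's own rating, and only rescue could expose it.

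A third reply is that the protocol does not say whether rescue is visible to a surgeon working at a covered patient. This also stands, so rescue can reveal the arm but need not.

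A reader might infer that observer blinding fails for the whole trial, including block grading. The order of events does not support that. A reader might also infer that rescue unblinds five times as often in the IVRA arm, from 12.5 / 2.5. That ratio is for grades 3 and 4 combined and carries over to grade 3 only if its share of incomplete blocks is the same in both arms, which the protocol does not state.

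**Conclusion.** The point holds for secondary outcomes only. The protocol contradicts itself on the start-of-technique score. If the researcher takes that score when it is defined, the arm is exposed in all 100 patients before the other patient-questioned outcomes are collected, with a direct breach of the stay-out rule in the IVRA arm alone. This assumes that the researcher, the assessor and the study assistant named in different sections are the same role.

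The rescue route is smaller: at most about 15 of 100 patients in expectation on the plan's rates, with the grade 3 share unknown. It can reach both researcher and surgeon. Block grading by the surgeon is untouched by either route.

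**What to change.** 1. Have the anaesthesiologist performing the technique, who already knows the arm, record the start-of-technique score on a sheet withheld from the researcher. In the Peri-operative phase section, except this item from the statement that the blinded researcher collects all secondary outcomes. Cost: protocol wording and one form, no extra staff. The downside is that one score is taken by an unblinded clinician, which should be reported.

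2. Reconcile the Peri-operative phase section with Randomisatie en blindering on how surgeon and researcher stay blinded when grade 3 rescue is given, leaving the rescue itself unchanged. Where this is not feasible, record the unblinding for that patient and limit the claim of observer blinding for that patient's later secondary outcomes. Cost: wording and one field on the case report form; the downside is a narrower blinding claim for those patients.
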